In patients with asthma, a therapy known as breathing control training (BCT) improves hyperventilation symptoms as shown on the Nijmegen scale of hyperventilation, anxiety and depression scores, and quality of life, but does not affect measures of airway function.^16^ We hypothesise that the same therapy when used for FS will improve breathing control, reduce hyperventilation and thus reduce the frequency of episodes. A standard course of BCT takes a single 1-hour session and a half-hour ‘refresher’ session at 1 month, administered by a physiotherapist. Its resource cost is substantially less than psychological interventions, which require several sessions, often more, by a specialised clinical psychologist. Even if BCT is effective in only a subset of patients, then it is likely to be very cost-effective, especially if we are able to determine which subset is likely to respond. BCT has the further advantage that it is likely to be acceptable to patients who may be deterred by psychological interventions, as it does not require that the patient frame or reframe their disorder as psychiatric.

We conducted a multisite, open-label, single-arm, pilot trial of BCT in FS.^17^ Participants with FS over the age of 16 years received an hour of breathing training from a respiratory physiotherapist, with a half-hour booster session a month later. Seizure frequency and Nijmegen scores (a measure of hyperventilation) were reported at baseline and follow-up, 3–4 months later. 18 subjects were recruited, and 10 completed follow-up. 7 of these 10 had improved seizure frequency, of which 3 achieved seizure remission, and 3 did not, with seizure frequency correlating with Nijmegen score (Spearman’s rank correlation=0.75). The intervention was well tolerated, with no adverse events (AEs) reported.

This provides preliminary data that BCT may be safe and effective for this patient group. This protocol is for a multicentre, randomised controlled trial to confirm these results.

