### Study hypothesis

We hypothesise that the proportion of patients with seizure remission, defined as FS frequency of zero in the preceding 4 weeks (recorded by the participant in a seizure frequency diary) at 12 weeks after initial treatment will be higher in the group of patients randomised to BCT compared with those randomised to control (Befriending).

Further, BCT will be as acceptable to patients and cost-effective compared with standard care for FS. In addition, we hypothesise that quality of life, work and social functioning, depression and anxiety symptoms, and hyperventilation tendency will improve more with BCT than control.

As an exploratory hypothesis, we expect hyperventilation preceding or during seizures will predict response to BCT, and that hyperventilation measured by expired carbon dioxide (CO_2_) will be clinically identifiable (by association with convulsive seizure phenomenology, childhood trauma history and increasing pre-ictal heart rate).

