Box 1OutcomesPrimarySeizure remission, defined as seizure frequency of zero in the preceding 4 weeks (recorded by the participant in a seizure frequency diary), measured at Week 12 (12 weeks post the initial treatment session).SecondaryChanges in hyperventilation from baseline, measured by the Nijmegen scale of hyperventilation provided at baseline, Week 4, Week 12 and Week 24.Changes in healthcare utilisation from baseline, measured via a tailored resource use questionnaire provided at baseline, Week 12 and Week 24, as well as changes in health service use ascertained from Services Australia and CVDL data (Services Australia and CVDL data for consenting participants only).Changes in quality of life from baseline, measured by the Assessment of Quality of Life Eight Dimension provided at baseline, Week 4, Week 12 and Week 24.Changes in depression and anxiety symptoms from baseline, measured by the 9-item Patient Health Questionnaire and Generalised Anxiety Disorder Assessment respectively, provided at baseline, Week 4, Week 12 and Week 24.Changes in occupational and social functioning from baseline, measured by the Work and Social Adjustment Scale provided at baseline, Week 4, Week 12 and Week 24.Acceptability of BCT captured by a tailored self-report questionnaire provided after attending the Week 4 ‘booster’ session.Safety of BCT assessed by the occurrence of adverse events reviewed at Week 4, Week 12 and Week 24.tcCO_2_ levels (mm Hg; a marker of hyperventilation) preceding or during seizures, BPAT score (at baseline) and/or Nijmegen score (at baseline), to predict response to treatment.ExploratoryThe presence of significant life events in childhood and adolescence (≤16 years of age), and 12 months preceding the onset of their FS, assessed via the Childhood Experience of Care and Abuse Questionnaire and the LEDS*, respectively, to gauge moderators of treatment response.The MDI and Toronto Alexithymia Scale provided at baseline will be assessed if predictors of treatment response. MDI scores at Week 4, Week 12 and Week 24 will be assessed if they correlate with treatment response.*Note, the LEDS is optional, and only relevant to participants whose FS have started within the last 2 years.BCT, breathing control training; BPAT, Brompton Breathing Pattern Assessment Tool; CVDL, Centre for Victorian Data Linkage; FS, functional seizures; LEDS, Life Events and Difficulties Schedule; MDI, Multiscale Dissociation Inventory; tcCO_2_, transcutaneous carbon dioxide.

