Box 2Trial schematicClinical assessment (neurologist)Functional seizures diagnosis confirmed by epileptologist.Participant informed of trial.Informed consent obtained OR obtain consent for study staff to follow-up and discuss.PrescreeningEligibility confirmed using prescreening questionnaire.Informed consent (if not completed by referring clinician).Baseline study questionnaires completed: Demographics, The Assessment of Quality of Life Eight Dimension (AQoL-8D), Generalised Anxiety Disorder Assessment (GAD-7), Patient Health Questionnaire, 9-item (PHQ-9), Multiscale Dissociation Inventory (MDI), Nijmegen, Toronto Alexithymia Scale, Resource Use Questionnaire (RUQ), Seizure triggers and control, Seizure quality, Work and Social Adjustment Scale (WSAS).Medical record data extracted.RandomisationPhysiotherapist contacts participant to inform them of their group allocation and schedule first session.Initial treatment session (Breathing Control Training/Befriending): baseline60 min, one-on-one session with physiotherapist, conducted at clinical care site (or Telehealth if required).Seizure frequency and adherence diary provided.Booster treatment session (Breathing Control Training/Befriending): week 430 min, one-on-one session with physiotherapist, conducted at clinical care site (or Telehealth if required).Adverse events, seizure frequency and adherence diary reviewed by physiotherapist.Research assistant (blinded) sends self-report questionnaires to participant via Research Electronic Data Capture (REDCap): *AQoL-8D, Acceptability, GAD-7, PHQ-9, MDI, Nijmegen, Seizure quality, WSAS.*Primary endpoint: week 12Research assistant (blinded) sends participant self-report questionnaires via REDCap: *AQoL-8D, Childhood Experience of Care and Abuse Questionnaire, GAD-7, PHQ-9, MDI, Nijmegen, RUQ, Seizure triggers and control, Seizure quality, WSAS.*Adverse events and medication status reviewed by research assistant.For eligible and willing participants, invited to complete Life Events and Difficulties Schedule.Follow-up: week 24Research assistant (blinded) sends participant self-report questionnaires via REDCap: *AQoL-8D, GAD-7, PHQ-9, MDI, Nijmegen, RUQ, Seizure quality, WSAS.*Participants randomised into the Befriending (control group) offered access to the BCT intervention.Observational follow-up: week 52, week 78 and week 104 (optional)Participants sent self-report questionnaires via REDCap: *AQoL-8D, GAD-7, PHQ-9, MDI, Nijmegen, RUQ, WSAS, seizure frequency (for previous 4*

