##### Acceptability

Acceptability of the intervention will be determined via a series of questions standardised during our pilot study. Examples include, ‘I found the training easy to understand…easy to do…easy to remember’ etc and the participant will be provided with a 5-point Likert scale ranging from ‘Strongly agree’ to ‘Strongly disagree’ for each question. We will also include a free-text section enabling the participant to provide additional feedback about the treatment if desired. This questionnaire is estimated to take between 2–5 mins to complete.

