#### Secondary outcomes

Binary outcomes will be analysed similarly to the primary outcome; continuous outcomes will be analysed using a Longitudinal Data Analysis model.^37^ Any markedly skewed continuous outcomes will be transformed before analysis. The acceptability of BCT captured by a tailored self-report questionnaire provided after attending the Week 4 ‘booster’ session and adverse events will be reported by study group and visit.

The statistical models for the primary and secondary outcomes will provide valid inference in the presence of missing data if the missing data mechanism is missing at random.

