## Discussion

This study described the design and methodology of the first multicentre, randomised, assessor-blinded, two-arm, parallel-group efficacy and acceptability trial of BCT versus control in patients with FS. Despite increased research in interventions for FS, and an abundance of smaller studies suggestive of therapeutic effect, there remain no definitive, validated treatments.^10^ Once completed, this study will represent only the second appropriately powered, multicentre, randomised trial of an intervention for FS.^22^ We hypothesise that BCT will reduce the seizures and related symptoms of FS greater than a control intervention designed to provide no benefit.

BCT has been found to be safe and well-tolerated when provided to people with respiratory conditions.^25^ As a brief intervention, it should prove cheap to deliver, and as an allied health intervention, it may prove more acceptable than psychotherapy interventions, where large proportions will not participate or complete the intervention.^22^ Its efficacy in FS remains to be determined, as it has not been subject to a trial other than our own pilot.^17^

The mechanism of any effect remains to be determined, but the therapy was designed to address abnormal breathing patterns, particularly hyperventilation, and in our pilot study, improvement correlated with improvement in this. People with FS do commonly have abnormal breathing, not only around the time of their FS.^13^ There are a priori reasons to think the intervention may work in FS, in the same way that it has worked in asthma. A goal of this study is to explore the mechanism of any effect, particularly in regard to breathing pattern, whether measured by clinical observation of breathing patterns, questionnaires or CO_2_ measurements. If the intervention is only effective in a subgroup defined by its breathing pattern, we would hope to be able to identify it.

The large sample size and randomised placebo-controlled design are significant methodological strengths in the current study. A further strength is the assessment of clinical outcomes at prolonged follow-up. Previous clinical trials have produced impressive results at the end of the intervention, only for a substantial proportion to relapse in follow-up.^10^ A final advantage for this study is the heterogeneity of the sample. The broad inclusion and limited exclusion criteria mean that participants experiencing a range of psychiatric comorbidities will be eligible.

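### As worded, acceptability is rated only by people who attended the second of two sessions, so it describes session completers, and its hypothesis names a comparator the trial does not have

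*Protocol article*

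**What the plan says.** Box 1 (Outcomes) lists as a secondary outcome "Acceptability of BCT captured by a tailored self-report questionnaire provided after attending the Week 4" booster session. The Secondary outcomes paragraph of the statistical analysis repeats that it is "captured by a tailored self-report questionnaire provided after attending the Week 4" booster, and says it will be reported by study group and visit. The other self-report scales collected at Week 4 (Nijmegen, AQoL-8D, PHQ-9, GAD-7, WSAS) are tied in Box 1 to the week alone, with no condition on attendance.

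Table 3 (Measures) schedules the acceptability questionnaire once, in the booster column. Box 2 lists it only under the booster step, where the "Research assistant (blinded) sends self-report questionnaires to participant via Research Electronic Data Capture (REDCap") in one batch with the other scales. The Acceptability subsection says: "Acceptability of the intervention will be determined via a series of questions standardised during our pilot study". It describes Likert items and free text.

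The Study hypothesis states that "BCT will be as acceptable to patients and cost-effective compared with standard care for FS". The Study objectives instead set efficacy, acceptability and cost-effectiveness against Befriending. The Discussion says of BCT that "it may prove more acceptable than psychotherapy interventions, where large proportions will not participate or complete the intervention".

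**The concern.** The treatment has two sessions, so attending the booster means completing the sessions. A questionnaire given on that condition selects on a behaviour closely tied to what it is meant to measure. A participant who found the training unhelpful or unpleasant and did not return gives no rating. Nothing else in the article gives the form to that person.

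This matters because of the article's own argument. The Background and rationale and the Discussion both describe psychotherapy as failing on acceptability because patients do not take part in it or do not finish it. A rating from completers cannot show whether BCT does better on that count. A completer-only denominator also sits badly with the statement under Statistical analysis that every analysis follows intention to treat. Acceptability is in the trial's description of itself, in its objectives and in its hypothesis, so the result is likely to be quoted.

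The hypothesis has a separate fault. It compares acceptability with standard care. Both arms receive standard care, no arm receives it alone, and no acceptability data on it are scheduled, so the trial cannot test the comparison as worded.

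**Working it through.** **The plan's own figure.** The article gives no number for acceptability. Its only related calculation is the sample size for the primary outcome, which reproduces. With 40% versus 20%, two-sided 5%, 80% power, pooled variance and no continuity correction:

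n per arm = [1.960 × √(2 × 0.30 × 0.70) + 0.842 × √(0.40 × 0.60 + 0.20 × 0.80)]² / 0.20² = 81.2, rounded up to 82.

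82 / (1 − 0.25) = 109.3, rounded up to 110 per arm, 220 in total. The point below does not change this.

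**Size of the selection effect.** Let m be the share of the BCT arm not asked, pA the favourable rate in attenders, and pN the rate that non-attenders would have given. The reported figure is pA. The figure for the whole arm is (1 − m) × pA + m × pN. The difference is

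overstatement = m × (pA − pN).

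**Inputs.**
- pA = 80–90% and pN = 0–50% are assumptions; the article gives neither. The gap pA − pN therefore runs from 0.80 − 0.50 = 0.30 to 0.90 − 0 = 0.90.
- m = 10% is the ceiling of the BCT attrition cited under Sample size calculation and recruitment target.
- m = 25% is the planned drop-out in the same section. It is set for the Week 12 endpoint, so using it here assumes that all of it falls before the booster. That is an extreme case.
- m = 5% is an assumed low value.

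**Results.**

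| m | Of 110 in the BCT arm | Smallest (m × 0.30) | Largest (m × 0.90) |
|---|---|---|---|
| 5% | 5.5 | 1.5 points | 4.5 points |
| 10% | 11 | 3 points | 9 points |
| 25% | 27.5 | 7.5 points | 22.5 points |

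If non-attenders would have rated the training as attenders do (pN = pA), the overstatement is zero at any m.

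**Comparator.** Study objectives: acceptability against Befriending. Study hypothesis: acceptability against standard care. Trial design and Concomitant care: two arms, both on top of standard care. Secondary outcomes: reporting by study group. Three of these four fit a comparison with Befriending; the hypothesis does not.

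**The case against.** The strongest reply is that the attendance phrase may fix timing and not act as a gate. Box 2 has the blinded research assistant, not the physiotherapist, send the form in the same REDCap batch as the other Week 4 scales, and nobody would expect those to be withheld from people who missed the booster. This stands in part: the delivery route would allow the form to reach non-attenders. But the condition is written twice, it is attached in Box 1 to this questionnaire and not to the other scales in the batch, and no passage extends the form to people who miss the session. Read as written, it limits who is asked.

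A second reply is that related data exist: home-practice diaries (Adherence), a checklist after each session (Training and fidelity) and an exit interview on reasons for withdrawal (Participant safety and withdrawal). These help the fix. They do not fill the gap, because none is named as an acceptability outcome, the diaries exist for BCT only, and the interview may be declined. A third reply, that tables and handling of non-response belong in the analysis plan, is fair, but who receives the form is fixed here.

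A reader might infer an overstatement of 22 to 40 points by taking a 90% favourable rate in attenders, scoring every non-attender as not accepting, and using the planned 25% drop-out or the pilot's loss (0.90 × 0.25 = 22.5 points; 0.90 × 8/18 = 40 points). The documents do not support that range as an estimate. The pilot line, "18 subjects were recruited, and 10 completed follow-up", refers to follow-up at 3–4 months and not to attendance at a one-month booster; the 25% is a Week 12 figure that the article calls conservative; and people also miss sessions for reasons unrelated to the treatment.

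A reader might also infer that attendance and adherence should replace the questionnaire as the main measure. That is a preference for a different construct, and adherence cannot be compared between arms.

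**Conclusion.** The point holds as a selection problem in a secondary, descriptively reported outcome. Under the stated rule the acceptability rating comes from people who attended both sessions, and it cannot bear on the non-completion that the article presents as the problem to be solved.

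Upward bias is the expected direction, not an established fact. It requires non-attenders to think less well of the treatment than attenders do, and the documents give no data on that. On the assumed ratings, about 3–9 points at 10% non-attendance is the most relevant illustration, since 10% bounds the only BCT-specific attrition figure cited; 7.5–22.5 points is an outer case. People who dislike BCT but still attend the booster are counted, which limits the effect. The sample size and the primary analysis are untouched.

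The mismatch between hypothesis and objective on the comparator is a plain contradiction in the text and rests on no assumption.

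**What to change.** 1. Remove the attendance condition in Box 1 and in Secondary outcomes. State that the Week 4 acceptability form goes through REDCap to everyone who had the initial session, whether or not they attend the booster. People who never had a session should not get it, because items on how easy the training was to follow would mean nothing to them; the counts in step 2 cover them.
2. Beside the ratings and their response rate, report by arm, with all randomised as denominator: attendance at the initial session, completion of both sessions, and withdrawal. Keep the questionnaire as the acceptability measure.
3. Align the acceptability hypothesis with the objective, so that both compare BCT with Befriending.

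The cost is small. The REDCap batch already exists, attendance can be derived from the per-session checklists, and no sample size changes. The acceptability figure may come out less favourable. Recruitment opened in February 2024, so this would be a mid-trial change in how a secondary outcome is collected. The date of change should be recorded so that ratings gathered under each rule can be told apart.

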
### Sample size calculation and recruitment target

A total of 220 participants (110 per group) are required to detect a clinically relevant absolute risk difference of 20% or relative risk of 2 in the proportion of patients with FS remission between BCT (40%) and Befriending (20%) at Week 12 (80% power, 5% two-sided significance level, 25% drop-out). A remission rate of 14% with TAU has been demonstrated in our local population,^22^ but because Befriending may have some negligible effects, we have adopted a more conservative 20% remission rate for participants who are randomly allocated to the control arm. 40% FS remission at Week 12 (primary endpoint) in the active arm was chosen as the clinically significant aim of being twice the proportion typically achieving remission with current psychotherapies such as cognitive behavioural therapy.^22^ The dropout rate is a conservative estimate as we have achieved much lower with this population in other trials,^23^ and BCT has attrition of less than 10%.^24^

### Recruitment

Recruitment commenced in February 2024 is expected to remain open for a period of 4 years. Participants will be recruited from their clinical care site (Austin, Alfred, RMH, SVHM or Christchurch), either as an inpatient or outpatient, following their diagnosis of FS. Patients with FS who have previously received care at the hospitals (as an outpatient/inpatient) may also be contacted via letter from the site PI and followed up by telephone to gauge interest in study participation.

Following referral to the trial by their clinical care team (while a patient, or via study invitation letter), a member of the research team will contact the candidate to discuss the trial and address any of their queries. If willing, the candidate will be taken through a prescreening questionnaire to assess their eligibility for the trial (ascertaining age, FS diagnosis and frequency, epilepsy diagnosis, current treatments/therapies). If the criteria are satisfied, they will be provided a copy of the consent form and asked to review and then followed up by study staff at a time of their convenience. If willing to proceed with the trial, written, informed consent will be obtained and additional baseline data collected (participant’s medical history, including psychiatric history, presence of functional disorders and asthma). The participant will be asked to complete baseline self-report questionnaires via REDCap prior to randomisation into the trial (see ‘Allocation’ section below). As per hospital/government or health authority guidelines, the trial can be administered via Telehealth if needed, without significantly compromising efficacy of the intervention,^24 25^ and thereby limit potential disruptions to recruitment.

Recruitment from both inpatient and outpatient sources may lead to recruitment of a more chronic, and thus possibly more refractory, sample, but will increase the number of potential recruits and enhance generalisability.

